### Aims and Objectives

There is a need to enhance academics’ well-being, yet effective, research-based, and feasible tools are limited. Accordingly, this study pursues 4 goals. First, we aim to develop an online ACT-based intervention for academic staff that integrates working-life skills, specifically time management and reflective skills, and is feasible to complete within demanding work environments. Second, we aim to evaluate the intervention quantitatively by identifying latent burnout profiles among university staff and examining whether changes in burnout, psychological flexibility, perceived stress, overall well-being, and procrastination differ across profiles and participation formats. Third, we aim to examine participant engagement and retention by investigating whether dropout differs across latent burnout profiles and according to participation formats (individual vs group-based). Fourth, we aim to explore participants’ lived experiences of the intervention qualitatively, with a particular focus on psychological flexibility processes and on which of these processes’ participants perceive as most meaningful for their well-being and functioning at work.

Our research questions (RQs) are as follows:

RQ 1. What latent burnout profiles can be identified among staff at the University of Helsinki, and to what extent do the effects of the online ACT-based intervention differ between them?RQ 2. How do observed pre-post changes in burnout, psychological flexibility, perceived stress, and overall well-being vary across burnout profiles and participation formats?RQ 3. How do latent burnout profiles differ in training dropout rates, and does participation in group-based versus self-guided online ACT-based training relate to dropout?RQ 4. How do participants describe their experiences of psychological flexibility processes following participation in a digital ACT-based intervention, and which of these processes do they perceive as most meaningful in supporting their well-being and functioning in their work?

## Methods

### Study Design

#### Mixed Methods Design

We will conduct a single-arm, nonrandomized, and mixed methods study with baseline, post-intervention, and 6-month follow-up assessments. Our study methodology description is based on the GRAMMS (Good Reporting of a Mixed Methods Study) reporting guidelines [38] and checklist (Checklist 1). A mixed methods approach is chosen, as the study aims to evaluate changes in participants’ well-being and related outcomes at the group level and to understand how participants experienced the intervention and its psychological flexibility processes at the individual level. An explanatory sequential design will be used, with priority given to the quantitative strand. Quantitative data will address latent burnout profiles (RQ 1), changes in outcomes, and dropout (RQs 2 and 3), whereas qualitative data will be used to explain, contextualize, and deepen these findings by examining participants’ final reflections, goal statements, and interview accounts (RQ 4). Although some qualitative material is generated during the course, qualitative interviews will be conducted after the main quantitative data collection phase.

Integration will occur at the interpretation stage once all data have been collected. Integration will be conducted by the researchers, involving the comparison and combination of quantitative findings (RQs 1‐3, changes in outcomes, burnout profiles, and dropout) with qualitative data (RQ 4, participant reflections and interviews). Through this, we will explore how quantitative patterns are potentially explained and contextualized by participants’ individual experiences, as well as identify possible convergence, complementarity, or divergence between the 2 data strands.

#### Setting and Participants

This study is conducted at the University of Helsinki where the course is open to all university personnel, including teaching faculty, researchers, and administrative and support staff. The course has been available since fall 2023. For RQs 1 to 3, participants are recruited to attend the course via regular communications and advertisements to university personnel via university HR, intranet, email, and website. All willing participants can attend the course, and there are no exclusion criteria in the study. Participation in the research is optional, and participants can study in the course without consenting to research. At the beginning of the course, participants are asked to give or decline their permission to use their questionnaire data and written responses for research purposes.

For RQ 4, a purposive subsample (N≈30‐40) will be recruited from participants who have completed the course for semistructured interviews. Sampling will be stratified according to the latent burnout profiles identified in RQ 1 in order to include participants from each profile and permit systematic comparison of experiential patterns across profiles. Separate written consent is given for the interviews before the start of the interview.

For RQs 1 to 3, data collection started in 2023 when the course was opened to all staff members. For RQ 4, data collection is scheduled to take place in fall 2026.

### The Course

The course “Occupational Well-being for University Staff” is based on ACT, with a central aim of enhancing participants’ skills in psychological flexibility. Training in key working life skills, such as time and effort management and reflection, is integrated into the course. The course was developed on the web-based Moodle platform and can be completed entirely online. Although it is recommended to complete the course over a 12-week period, participants are free to proceed at their own pace. The flexible schedule is an attempt to accommodate the varying time demands of academic work and allow participants to engage with the course at times that best suit their individual schedules. Participants can take the course either with a group or on their own. A group can be, for example, a research group, a team, or a unit. The small group discussions in the course work best if there are 3 to 5 people in the group, but participants can choose how to conduct this. The course is designed to function without a facilitator.

### Course Modules

The course consists of 6 modules. Each module includes all necessary materials, such as instructions, short video lectures, practical exercises, reflective assignments, and guidance for peer discussions. The course is structured so that participants complete 1 module at a time.

#### Introductory Part

In the beginning of the course, the participants are introduced to the working in the course and informed about the research concerning the course. The research permit is also asked in the beginning. In addition, the participants are asked to answer questionnaires concerning their well-being and working skills, from which they receive feedback.

#### Module 1: Time Management

This module includes an introduction to the concept of psychological flexibility and a time management exercise in which participants are instructed to track their time use for a week. This exercise and the insights gained from it serve as a foundation for several reflective assignments throughout the course.

#### Module 2: Values

This module consists of materials and exercises that are related to one’s values and includes exercises that help participants to explore their values and think about the issues that are important for them. Participants can choose from a variety of exercises the ones that best suit them, and all exercises have been designed to help participants to recognize the issues and things that are important for them and to reflect on different areas of their lives and their current level of satisfaction with each. Based on this reflection, they are asked to formulate a personal goal for the course.

#### Module 3: Recognizing Thoughts

This module is focused on identifying one’s thoughts and understanding their effects on behavior. Procrastination, its influence on behavior, and strategies to overcome it are also discussed. Participants can choose from a variety of exercises tailored to their needs.

#### Module 4: Focusing on the Present Moment

This module emphasizes the importance of being able to concentrate on the present and develop awareness of one’s current feelings and emotions. Participants are encouraged to confront all varieties of their emotions, including negative ones, with acceptance and curiosity. Additionally, stress, its effects, and strategies to overcome it are discussed in this module.

#### Module 5: Self-Compassion

This module focuses on self-compassion, comprising themes related to self-kindness, acceptance, and the self as context. Participants are also encouraged to cultivate a thankful attitude in their daily lives and practice compassion toward their peers.

#### Module 6: Committed Action

The last module is related to committed actions and addresses how one’s values can be concretely translated into action. As a weekly assignment, the participants are asked to reflect on value-based actions in their lives according to the square field below (Figure 1)—thinking about their actions, emotions, and thoughts toward meaningful actions. Participants are instructed to consider how they will move forward after the course and what new goals they might set for themselves. In addition, the participants assess their well-being and working skills again and are encouraged to reflect on their change in the scores and overall development during the course.

**Figure 1. F1:**
[figure not shown]
Square field for value-based actions.

### Measures and Data Collection

#### Quantitative Data

First, for RQs 1 to 3, validated self-assessment questionnaire data will be collected before (T1), after (T2), and 6 months after the course (T3). The questionnaires measure emotional, psychological, and social well-being (Mental Health Continuum-Short Form) [39]; psychological flexibility (Work-related Acceptance and Action Questionnaire) [40]; perceived stress (Perceived Stress Scale) [41]; and risk of burnout (15-item Bergen Burnout Indicator) [42]. Psychometric properties will be further evaluated in the present sample via internal consistency (Cronbach α) and factor structure (confirmatory factor analysis). A 6-month follow-up is used to examine how potential changes during the course persist or change over time. Psychological flexibility especially is understood as a process that develops gradually through ongoing practice and integration into daily life, and changes may therefore continue to evolve beyond the course period [21]. Furthermore, this timeframe is also consistent with prior research in the field, which commonly uses follow-up periods of 6 months [43-45].

#### Qualitative Data

Subsequently, for RQ 4, the study will use qualitative data to deepen insights derived from quantitative data. Data will be collected from (1) participants’ written final reflections submitted on the course platform, (2) participants’ written goal statements completed at the beginning and end of the course, and (3) semistructured interviews conducted after the end of the course.

In the beginning, the participants are asked to analyze and identify what factors cause them stress in the workplace or in life and how they could affect it. They are also asked to set a value-based goal which they focus on during the course. At the end of the course, participants write a final individual reflection on how they experienced the course, how the course affected their well-being and working life, how they achieved their goal, and how they are planning to go forward.

Semistructured interviews will examine participants’ experiences of psychological flexibility processes following participation in the intervention, with particular attention to which processes are perceived as most meaningful in supporting well-being and functioning in academic work. The interview guide will be informed by the ACT model and will address core psychological flexibility processes, including acceptance, cognitive defusion, present-moment awareness, self-as-context, values clarification, and committed action, while allowing participants to elaborate on how these processes were experienced and applied in their work context.

### Analyses

#### Statistical Analyses

For RQ 2, the effects of the course are analyzed with repeated-measures ANOVA and hierarchical modeling to see the changes at the group level. In addition, for RQ 1, the participants will be clustered based on their initial burnout risk score to compare the effects of the course in different risk groups using latent profile analysis and repeated-measures ANOVA. For RQ 3, attrition analyses are conducted using chi-square tests of independence and odds ratios to examine whether dropout rates differ across latent burnout profiles and between group-based and self-guided participation formats.

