**Methods:**

We will conduct a single-arm, nonrandomized, and mixed methods study with baseline, postintervention, and 6-month follow-up assessments. We will use an explanatory sequential design in which qualitative data are used to explain and deepen the quantitative findings. The quantitative part of the study aims to recruit 300 participants from the University of Helsinki. Questionnaire data will be collected from the participants 3 times: at the beginning, at the end, and 6 months after the course for well-being–related measures such as burnout and working life skills such as time management and psychological flexibility. The participants will be clustered based on their initial burnout risk score using latent profile analysis. Differences in participants’ dropout, participation forms, and changes in well-being and working life skills during the course will be analyzed with mixed ANOVA. Qualitative data will be collected from reflective journals written at the end of the course, participants’ written goal statements, and interviews among willing participants. Reflective journals will be analyzed with qualitative content analysis, and interviews will be analyzed using thematic analysis.

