## Results

As of the first data freeze in November 2025, a total of 265 participants had enrolled in the course and given their consent to participate in the research, and 113 participants have completed the course (Table 1). Among participants who completed the course, the mean number of days between questionnaires at T1 and T2 was 123, and the median was 109 days. The first data cut is expected to be published in late 2026 or early 2027. Preliminary results suggest that participants’ burnout scores at T1 reflect 3 distinct profiles and that the profiles experiencing the highest burnout scores are also more likely to drop out. Similarly, participants completing the course alone were more likely to drop out than those in a peer group.

**Table 1. T1:** Characteristics of the study sample recruited in the first data cut (N=265).

Background characteristics	Participants, n (%)
Job description	
Teaching and research staff	35 (13.2)
Other expert and support staff	226 (85.2)
Missing or N/A^a^	4 (1.5)
Course completion method	
Self-guided or alone	99 (37.4)
With a peer group	145 (54.7)
Missing or N/A	21 (7.9)

a N/A: not available.

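### Change is to be analysed by repeated-measures or mixed ANOVA (alone for RQ 1 and in the abstract), although completion is 43% and related to burnout profile and format, which puts the overall change at material risk of bias

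*Protocol article*

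**What the plan says.** The protocol article names methods for the analysis of change in three places.

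- **RQ 2 (Statistical Analyses):** "the effects of the course are analyzed with repeated-measures ANOVA and hierarchical modeling to see the changes at the group level". Two methods stand side by side and neither is named as the lead.
- **RQ 1 (Statistical Analyses):** the aim is to "compare the effects of the course in different risk groups using latent profile analysis and repeated-measures ANOVA". No hierarchical model is mentioned.
- **Abstract, Methods:** "changes in well-being and working life skills during the course will be analyzed with mixed ANOVA". No hierarchical model is mentioned here either.

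Questionnaires are collected "before (T1), after (T2), and 6 months after the course (T3"). In the description of Module 6, the last module, "the participants assess their well-being and working skills again", so T2 is part of finishing the course. T3 is timed from the end of the course.

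The Results section reports 265 consenting enrolees and 113 completers at the November 2025 data freeze. It adds that "the profiles experiencing the highest burnout scores are also more likely to drop out", and that those working alone dropped out more often than those in a peer group.

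**The concern.** A conventional repeated-measures or mixed ANOVA analyses only people who have every wave in the model. As the course is described, someone who stops before Module 6 provides T1 and nothing else, so each course dropout is lost from the analysis of change. The article itself reports that these losses are not spread evenly over burnout profile and format.

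A simple mean change among completers therefore describes a group with lower baseline burnout, and more peer-group members, than the people who enrolled. Regression to the mean matters here: people with low T1 burnout tend to drift up and people with high T1 burnout tend to drift down. When the second group leaves more often, the completers' mean understates improvement. If instead people leave because they are not improving, the error runs the other way.

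RQ 3 studies dropout as an outcome, but the article does not carry that information into the analysis of change. With two methods listed for RQ 2 and no lead, the two could disagree and the choice could be made after the results are seen.

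**Working it through.** **Inputs from the article.** 265 enrolled with consent; 113 completed; three waves; T2 in the last module; more dropout with high burnout and with solo participation (no rates given).

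**Assumed inputs, not in the article.** True T1-T2 change -0.20 SD in everyone enrolled; T1-T2 correlation r of 0.6 to 0.7; equal SDs; normally distributed baseline burnout; T3 return of 60 to 80% among completers; three profiles with shares 35/40/25%, cut from the baseline score.

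**1. Completion.** 113/265 = 42.6%. Not completed: 152/265 = 57.4%.

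**2. Pooled completers, dropout rising with baseline burnout.** If m is the completers' mean T1 in SD units, their expected change is -0.20 - (1 - r) x m. With dropout log-odds of 0.4 per SD and 42.6% completing overall (about 55% in the lowest baseline quartile, 31% in the highest), m = -0.221.

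- r = 0.6: -0.20 + 0.4 x 0.221 = -0.112
- r = 0.7: -0.20 + 0.3 x 0.221 = -0.134

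Simulation of the same set-up gives -0.11 to -0.14. At log-odds 0.8, m = -0.403 and the change is -0.04 (r = 0.6) to -0.08 (r = 0.7).

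**3. Pooled completers, dropout depending on profile only.** Profile mean T1 values are -1.058, 0.132 and 1.271. With completion of 55/43/25%:

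m = (0.35 x 0.55 x -1.058 + 0.40 x 0.43 x 0.132 + 0.25 x 0.25 x 1.271) / 0.427 = -0.238

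The change is -0.10 (r = 0.6) or -0.13 (r = 0.7). With a milder gradient of 50/43/32%, m = -0.143 and the change is -0.14 or -0.16.

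**4. Within profiles.** If dropout depends only on profile, completers' change within each profile equals that of everyone in the profile, and weighting by enrolled shares returns -0.20. If dropout depends on the continuous baseline score at log-odds 0.4, within-profile error is 0.01 to 0.03 SD and the share-weighted change is -0.18 to -0.19. At log-odds 0.8, within-profile error reaches about 0.05 SD.

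**5. Likelihood fit on all available data.** Simulation with 265 people, three waves, true change -0.30 SD, r = 0.6, and 70% of completers returning T3:

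| Dropout mechanism | Three-wave complete cases | Likelihood fit |
|---|---|---|
| Baseline, log-odds 0.3 per SD | -0.23 | -0.30 |
| Baseline, log-odds 0.5 | -0.19 | -0.30 |
| Baseline, log-odds 0.8 | -0.14 | -0.30 |
| Baseline 0.5, plus unseen T2 0.5 | -0.37 | -0.48 |

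**6. Precision.** A T1-T2 ANOVA keeps at most 113 people, with a standard error sqrt(265/113) = 1.53 times that with all 265. A three-wave ANOVA at 60 to 80% T3 return keeps 113 x 0.6 = 68 to 113 x 0.8 = 90, and the T1-T2 standard error is sqrt(1/0.8) = 1.12 to sqrt(1/0.6) = 1.29 times that from all 113. In the simulation the standard error was about 0.10 for three-wave complete cases, 0.08 for the likelihood fit and 0.055 with no missing data.

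**The case against.** **Hierarchical modeling is already named for RQ 2.** This stands. Fitted by likelihood to all available data, it would keep people with T1 only. A reader might infer that ANOVA is the sole analysis of change; for RQ 2 the article does not say so. RQ 1 and the abstract, however, offer no such alternative.

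**An article leaves missing-data detail to the full plan.** True, and the absence of such detail is not the point. The article names a particular method, and its own Results section shows why that method is a poor choice.

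**Bias does not follow from dropout by profile and format.** A reader might infer that every estimated change is biased. Step 4 shows otherwise: where profile and format are factors in the model and dropout depends only on them, within-cell change is unbiased. The problem lies mainly in change averaged over the sample, which RQ 2 also seeks.

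**57% is not final dropout.** This stands. The course is continuously open and self-paced, with a median of 109 days from T1 to T2 among completers, so some of the 152 may still be in progress.

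**The lost precision is mostly not due to ANOVA.** This stands for T2: no model recreates scores that were never collected. What ANOVA adds is the loss of completers who lack T3, if all three waves enter together.

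**The mixed model can do worse.** It can. In the last row of step 5 the likelihood fit is further from -0.30 than complete cases are, which is why a sensitivity analysis belongs with it.

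**The article admits selection bias and limited conclusions on effectiveness.** It does, but that caveat does not repair the choice of analysis.

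**Conclusion.** The point holds for the overall group-level change. Complete-case ANOVA is a weak stated method when 113 of 265 have completed and completion is reported to vary with burnout profile and format. Under the assumed inputs, a true change of -0.20 SD would appear as about -0.11 to -0.13 SD in pooled completers, a loss of roughly a third to somewhat under a half. That figure applies to an unstratified mean change in burnout only. It should not be read as the error in profile-specific change, which is about 0.00 to 0.03 SD under the same inputs.

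The true effect, correlation, dropout gradient, profile shares and T3 return are all assumptions; the article gives none of them. The direction of bias is not established: baseline-dependent dropout understates improvement, and dropout that depends on later outcomes can overstate it. The supported statement is a material risk of bias, not demonstrated bias.

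**What to change.** - Name one likelihood-based linear mixed model as the lead analysis for both RQ 1 and RQ 2. Use every consenting participant with T1, keep T1 as an outcome, treat time as categorical with unstructured covariance, and include profile, format and their interactions with time.
- Report the overall change averaged over the enrolled shares of profile and format.
- Keep ANOVA as a secondary analysis, labelled as completers only.
- Bring the abstract into line with the Statistical Analyses section.
- Add a delta-adjusted sensitivity analysis for dropout that depends on unseen outcomes.

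The cost is a change of wording and a little more modelling, since hierarchical modeling is already planned for RQ 2. Two burdens remain: the lead analysis rests on a missing-at-random assumption, and format is missing or not available for 21 of 265 (7.9%, Table 1), so the plan must say how those people stay in the model.

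Sending T2 and T3 questionnaires at fixed times regardless of completion is not part of this fix. It would change what T2 means in a self-paced course.

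### The Methods name no analysis of change by participation format, which RQ 2 asks for; they name no dropout analysis containing both profile and format; and the abstract contradicts them on how dropout is analysed

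*Protocol article*

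**What the plan says.** **The questions.** In the protocol article, Aims and Objectives, RQ 2 reads: "How do observed pre-post changes in burnout, psychological flexibility, perceived stress, and overall well-being vary across burnout profiles and participation formats". The second aim makes the same comparison and extends its outcome list to whether changes in "procrastination differ across profiles and participation formats". RQ 3 asks about dropout by profile and by format.

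**The analyses in the Methods.** Under Statistical Analyses, each question receives one sentence:
- RQ 2: "the effects of the course are analyzed with repeated-measures ANOVA and hierarchical modeling to see the changes at the group level".
- RQ 1: participants are grouped by initial burnout risk "to compare the effects of the course in different risk groups using latent profile analysis and repeated-measures ANOVA".
- RQ 3: "attrition analyses are conducted using chi-square tests of independence and odds ratios", applied to latent profiles and to group-based versus self-guided participation.

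**The abstract.** Its Methods paragraph says that differences in participants' "dropout, participation forms, and changes in well-being and working life skills during the course will be analyzed with mixed ANOVA".

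**The data so far.** The Results section reports 265 consenting participants, of whom 113 had completed. Table 1 lists 99 taking the course alone, 145 with a peer group, and 21 with format missing or not available. The same section reports preliminary findings that the highest-burnout profiles, and participants working alone, were more likely to drop out.

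**The concern.** A stated question should be traceable to a stated analysis. Here the sentence assigned to RQ 2 gives a purpose, aggregate change, that differs from the question, which is a comparison between subgroups. Format is written into the RQ 3 sentence but not the RQ 2 sentence, so the omission falls where the question needs it.

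Two things are at stake. First, if the paragraph is followed literally, the format half of RQ 2 gets no estimate, and any format comparison of change would be specified after preliminary profile and format results have been seen. Second, profile and format are both reported as related to dropout, and participants choose their own format. If the two overlap, tests of each factor by itself cannot show whether working alone adds anything to high initial burnout. The Strengths and Limitations section wants practical information on how, and for whom, the course is most beneficial, so the overlap matters for interpretation.

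**Working it through.** The plan gives no numerical figure on this point to reproduce. The check sets each question against its assigned analysis.

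**Step 1. Mapping questions to analyses.**

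| Comparison asked for | Named in Statistical Analyses? |
|---|---|
| Change by profile (RQ 1, RQ 2) | Yes, under RQ 1 |
| Change by format (RQ 2) | No |
| Dropout by profile (RQ 3) | Yes, chi-square and odds ratios |
| Dropout by format (RQ 3) | Yes, chi-square and odds ratios |

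One of four comparisons is unnamed. The abstract mentions participation forms beside mixed ANOVA, but lists them among the things analysed and does not name them as a between-subject factor.

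**Step 2. Meaning of the group-level phrase.** It might be read as referring to peer-group participation. The Mixed Methods Design section rules that out: it speaks of "related outcomes at the group level and to understand how participants experienced the intervention" and sets this level against the individual one. The phrase means the aggregate.

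**Step 3. Dropout method.** The abstract says mixed ANOVA; the Methods say chi-square tests and odds ratios. Dropout is recorded once per participant as yes or no. A mixed ANOVA of repeated scores does not fit it, whereas the Methods choice does. Both statements cannot stand.

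**Step 4. Is a format comparison feasible?** Format is known for 99 + 145 = 244 of 265 (92.1%) and missing for 21 (7.9%). Of the 244, 99/244 = 40.6% took the course alone. Completed: 113/265 = 42.6%; not completed: 152/265 = 57.4%, some of whom may still be in progress.

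**Step 5. Illustration of overlap in the dropout analysis.** The document gives no profile sizes, no dropout by profile and no format by profile, so every input here is an assumption: low/mid/high profile shares of 35/40/25%; dropout of 45/58/72%; and no format effect within any profile.

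- *Alone in 30/40/55% of low/mid/high.* Share alone = 0.35×0.30 + 0.40×0.40 + 0.25×0.55 = 0.4025. Dropout alone = (0.105×0.45 + 0.160×0.58 + 0.1375×0.72)/0.4025 = 0.594. Dropout with peers = (0.245×0.45 + 0.240×0.58 + 0.1125×0.72)/0.5975 = 0.553. Crude odds ratio = (0.594/0.406)/(0.553/0.447) = 1.18.
- *Alone in 40% of every profile.* Both dropout rates are 0.5695; odds ratio 1.00.
- *Gradient reversed, 55/40/30%.* Dropout alone = (0.1925×0.45 + 0.160×0.58 + 0.075×0.72)/0.4275 = 0.546. Dropout with peers = (0.1575×0.45 + 0.240×0.58 + 0.175×0.72)/0.5725 = 0.587. Odds ratio = (0.546/0.454)/(0.587/0.413) = 0.85.

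Under these assumptions a crude odds ratio between 0.85 and 1.18 can arise with no format effect at all. The direction depends on who chooses to work alone, which the document does not report.

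**The case against.** The strongest reply is that this is an article, not the full analysis plan. It lists no model terms for any analysis. A hierarchical model can carry a format term, and a mixed ANOVA has a between-subject factor by definition. RQ 2 speaks of observed changes, and RQ 3 asks only whether format relates to dropout; crude comparisons answer descriptive questions. The limitations already concede non-randomisation and selection bias.

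Much of this stands, and it limits the point. A reader might infer that the stated analyses fail to answer the research questions in general. The document does not support that: RQ 3 is answered for each factor singly, and change by profile is covered. Nor does it support saying that format is excluded from the RQ 2 models; it is unnamed, not ruled out. The dropout tests are also not expressly described as separate or unadjusted, although that is the natural reading.

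A reader might further infer that a format comparison of change must be biased by regression to the mean. That is not established. No initial scores by format and no correlation between T1 and T2 are given, and if the self-selected groups differ stably, each regresses towards its own mean.

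What the reply does not remove is the mismatch within the article. The purpose stated for RQ 2 differs from its question, and no unseen plan can make both dropout statements true. The later text also wants more than a crude description: the discussion of time burden says the study will explore whether burnout scores and format contribute to dropout.

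**Conclusion.** The point holds in a limited form, with three parts:
1. The Methods assign RQ 2 an analysis of aggregate change and name no comparison of change by format.
2. The abstract's method for dropout contradicts the Methods and does not suit the outcome.
3. No named dropout analysis contains both profile and format, so the plan as written cannot show whether the two reported associations are separate or overlap.

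The first two rest on the text alone. The third rests on the natural reading of the RQ 3 sentence and on format being self-chosen. Its numerical consequence is unknown; the 0.85 to 1.18 range illustrates the mechanism under invented inputs and is not an estimate for this study. The correction is worth making because it is cheap and results are already being prepared.

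**What to change.** - **Statistical Analyses, RQ 2:** state one mixed model per outcome with time, profile, format, time × profile and time × format. Report the format contrast as an association, because participants choose their format. Adding job group or T1 burnout as main effects only would not help: without an interaction with time they leave the time × format contrast essentially unchanged.
- **Statistical Analyses, RQ 3:** keep the chi-square tests and crude odds ratios, and add one logistic model of dropout with profile and format together. Report the adjusted odds ratios beside the crude ones. As preliminary results have been seen, say when these analyses were specified.
- **Abstract, Methods:** take dropout out of the mixed ANOVA sentence and give the method stated in the Methods section.

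The cost is a few sentences and the analysis of variables already collected. The adjusted estimates will have slightly wider intervals, and the 21 of 265 participants without a recorded format drop out of the format terms unless the missing values are handled.
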